### Biological sampling and storage

For each case and control that agrees to participate to the blood sampling, two samples are collected at the inclusion by the investigators (1 × 7 ml EDTA (Ethylene diamine tetra-acetic acid) tube, 1 × 7 ml heparinized tube). Blood samples have to be centrifuged within one hour from sampling. For CECOS having -80°C storage, EDTA tube might be stored directly. For CECOS having -196°C storage only (all CECOS are equipped for sperm and egg conservation), buffy coat have to be extracted from the EDTA tube and stored in an adapted cryotube. Concerning the heparinized tube, plasma have to be extracted and stored in 1 ml aliquot in cryotubes at -80°C or -196°C depending on the equipment of each CECOS. Cryotubes are identified using the personal identification number attributed by the online study platform to each participant. Samples are gathered and shipped regularly using a specialized transporter to the Biological Resources Center (BRC) of Centre Léon Bérard (CLB), Lyon. At the BRC, DNA is extracted from the buffy coat (in case of -196°C preservation) or the EDTA tube (in case of -80°C preservation) using the AUTOPURE automaton (Quiagen, Germany). Then, DNA is stored at -80°C (300 ng DNA per aliquot).

### Data collection

Data from cases, controls and case/control mothers (or relative) are collected through a standardized phone questionnaire administrated by professional interviewers (IPSOS company). Interviewers are unaware of the case or control status of study subjects. To ensure consistency in data collection, interviewers have been trained in the completion of the questionnaire and provided with a field guide. All data are entered directly on the specially designed online study platform used for registration and data collection (for items, see Table 1). Investigators, technicians and researchers have a personal login and password to access the platform. Accesses to sensitive data are restricted, based on the user profile. The coordinating center contact the clinicians in charge of cases to obtain the pathology report and serum markers (alpha feto-protein, beta-HCG). For eligible subjects who refuse to participate, age, job, and reason for refusal are collected by investigators and entered into the study platform.

**Table 1 Tab1:** **Items collected during the phone interview**

Categories	Cases and controls	Mothers (or closest relatives)
General information	Medical history and long term treatments (childhood); Birth characteristics; Geographical origin; Socio-economic status	Medical history (mother); Treatments during pregnancy; Age and morphology at birth; Birth characteristics (son); Socio-economic status
Occupational exposures	Entire job history (+tasks and company name and addresses); Specific questions on pesticides, solvents, welding fumes, heavy metals and plastic exposures	Job history from the beginning to the 17 years of the son (mother)/job history from 1 year before the conception to the 17 years of the son (father); Specific questions on pesticides, solvents, welding fumes, heavy metals and plastic exposures
Environmental exposures	Whole residential history and households characteristics; Addresses of schools	Residential history from 1 year before son’s conception to the 17 years of the son
Domestic exposures	Domestic use of pesticides gardening, pet treatment, indoor usage of insecticides or fungicides, and lice treatment (at puberty)	Domestic use of pesticides gardening, pet treatment, indoor usage of insecticides or fungicides, and lice treatment (son: perinatal period and at puberty)
Lifestyle	Smoking status; Drug use; Physical activity	Smoking status; Drug use

### Occupational exposure assessment

Occupational exposure assessment of prenatal and early postnatal periods involve encoding parental occupations (mother: from the beginning of the job history to the 17 years old of the subject; father: from one year before conception to the 17 years of the subject). Based on the occupational history and job/task related information, all occupations are encoded by an industrial hygienist according to the International Standard Classification of Occupations (ISCO). The ISCO-68 is used to classify jobs of subject’s parents, and the ISCO-08 is used for the subject’s jobs. The French nomenclature of activity (NAF) is used to code the industrial classification of all jobs. In a second step, an industrial hygienist performs a detailed occupational exposure assessment based on job and task descriptions. Specific items have been added to the questionnaire to help the hygienist to assess exposures suspected to be associated with TGCT: pesticides, plasticizers, solvents, welding fumes and heavy metals. For each job held, probability, intensity (low, intermediate, strong) and duration of exposure are encoded.

### Domestic exposure assessment

Domestic exposure to pesticides is assessed for cases, controls and their mothers. Specific items in the questionnaire cover the main domestic pesticide use by interviewees and persons sharing the same household (gardening, pet treatment, indoor usage of insecticides or fungicides, and lice treatment), as well as the frequency of use. Pesticide exposure (compound family, probability of exposure and intensity) are estimated through expert assessment, based on the pesticide-use matrix developed by the National Cancer Institute (MD, US) [38].

### Environmental exposure assessment

Cases and controls residential history are gathered from 1 year prior to birth to date of the inclusion in the study. Semi-automatized fields in the study platform help to reduce misspellings when entering the questionnaire data. In case of inconsistency between subjects’ and mothers’ information, data provided by the mothers are used. Addresses are geocoded using the database “*BD adresse*” from the French National Geographic Institute (IGN), which contains coordinates of all addresses in France (unit: RGF Lambert 93). Since the coordinates of the database are centered on the postal address, a GIS technician moves manually the point to the center of the household. Using dedicated software (BD Adresse® for ArcGIS Locator), we identify all addresses geocoded with poor precision (at the street level or less) for manual verification or repositioning (when possible). Specific additional questions are added to the questionnaire to help the GIS technician when no street number is available (closest crossing road or point of interest).

The use of infra-red images, based on the greenness reflectance, has been used successfully in previous US studies to reconstruct land use data [39, 40]. Satellites images are available from the Landsat® program from 1972 with an 80 m spatial resolution and from the SPOT® program from 1986 with a 20 m spatial resolution. Based on remote sensing of satellite images and/or photo interpretation of IGN aerial photography (available from 1920’s), we determine the land use around each residence of interest. When data are not available or of poor quality, we assign land use data of the nearest available time period to the residence. Public data from agricultural statistics (Recensement Statistique Agricole, DRAAF) as well as expert assessment are used to validate our land use layer, when needed. The agricultural statistics provide the proportion of each type of crops in each municipality for 1970, 1979, 1988, 2000, and 2010.

The GIS based approach has been developed in a previous study (SIGEXPO project [41]). We investigated the link between environmental parameters (crop acreage, characteristics of neighboring cultivated fields, geographic and meteorological variables) and the concentration of pesticides in indoor dust of nearby homes. More than 700 samples were collected from 239 volunteer homes in the Rhône-Alpes region, France. These were distributed according to the different types of territories and according to different levels of intensity of theoretical exposure. Samples were taken during the main period of pesticides use according to the representative cultures of the Rhône-Alpes region (orchards, wine, cereals), reflecting the main application modes used in France (rotary atomizer, inflatable ramps, pneumatic sprayer, and motorized mist blower mounted on straddle tractors). According to this study, our GIS methodology is based on 500 meter and 1000 meters buffers, the frequency of the wind direction (data from Meteo France®), the presence of topographic barriers (BD Alti, IGN), vegetative barriers (BD Topo®, aerial photography and/or remote sensing), and structural barriers (BD Topo®, aerial photography and/or remote sensing). The score we developed (Agricultural Exposure Index (AEI)) estimates the intensity of exposure to the different crop types for each address/year.

Specific attention is given to locations during known or suspected critical lifetime periods in the etiology of TGCT (prenatal, early life, puberty). The AEI can be used as a surrogate of agricultural pesticide exposure level. In a second step, we use pesticides matrices to convert the crop exposure level into a pesticide exposure level, for each family of pesticides (or compound per compound, when available). These matrices contain the list of pesticides likely to have been used depending on the type of crop and period. Two matrices are currently under construction in France and might be used in our study: MATPHYTO (*Institut de Veille Sanitaire, France*) and PESTIMAT (*Institut de Santé Publique, d'Épidémiologie et de Développement, France*).

### Social deprivation and territorial indicators

To determine the impact of social deprivation on TGCT risk, using the Townsend index [42] and European Deprivation Index (EDI) [43], individual and territorial socio-economic data are collected to be included in the GIS. Territorial data are available from INSEE (French National Institute for Statistics and Economic Studies) at the IRIS scale (acronym for ‘aggregated units for statistical information’, covering a target size of 2000 residents per basic unit).

### Genetic analyses

We investigate polymorphisms known to be associated with TGCT risk. We identified 45 Single Nucleotide Polymorphisms (SNPs) revealed through 4 Genome Wide Association Studies and one replication study (from 8 loci: KITL, BAK1, SPRY4, ATF7IP, TERT, DMRT1, TGFBR3 and BMP7) [8, 44–47]. Associated odds ratios (OR) were 1.37 (95%IC 1.1 – 1.58, p = 10 e-13) for polymorphisms on chromosome 5; 1.50 (95%IC 1.28 – 1.75, p = 10 e-13) for polymorphisms on chromosome 6; and 2.55 (95%IC 2.05-3.19, p = 10 e-31) for polymorphisms on chromosome 12. Additionally, we identified 6 additional SNPs associated with organochlorine metabolism pathways and known to be able to modify the risk to develop a TGCT (2 loci: CYP1A1 and HSD17B4) [26]. Other polymorphisms may be added if new publications suggest additional polymorphisms prior to the genetic analysis. Considering rapidly decreasing costs of genetic analyses, a genome wide screening might become an alternative option for SNPs analyses.

### Determination of the sample size

Our research will examine the association between TGCT risk and occupational, domestic and environmental pesticides exposure. Since occupational pesticides exposure is supposed to be less frequent and associated with higher exposure levels than domestic and environmental exposures, we based our sample size calculation on the prevalence of occupational pesticides exposure among case and control parents. Based on the prevalence of agricultural workers in France in 1988 (10%) (http://agreste.agriculture.gouv.fr/IMG/pdf/AGRIFRA07c-2.pdf), the minimum detectable odds ratio with our sample (500 cases and 1000 matched controls) is 1.6, considering a statistical power of 80% at a significance level of 5%. Considering additional occupations associated with pesticides exposure (e.g.: greenhouse worker, sawmill worker, forester), the total prevalence of exposed workers should be higher. Considering a prevalence of exposure of 15%, the minimum detectable odds ratio under the conditions outlined above is 1.5.

### Statistical analyses

Standard descriptive statistics will be used to describe characteristics and pesticide exposure of cases, controls and mothers/relatives. Exposure variables will be explored using supervised principal component analyses [48]. Risk analyses will be based on conditional logistic regression models, to compute odds ratios for TGCT at different levels of exposure. Exposure variables will be investigated as continuous variables (with appropriate transformation to achieve normality) as well as categorical variables (quartiles or predefined categories depending on variable type). In addition we will create a combined pesticide exposure variable based on pesticide exposure (occupational, environmental and domestic) during prenatal and early postnatal period (PEPPP) and during adolescence (PEA). We will examine PEPPP exposure, PEA exposure, and combined PEPPP and PEA exposure in relation to TGCT risk. The effects of additional potential confounders (other than our matching criteria) on the associations between pesticide exposure and risk of TGCT will be examined and added to the model one by one. Comparison between models with and without adjustment will be used to examine the potential confounding effect of these factors and only factors with relevant changes in the odds ratios will be kept in the final model. Potential confounders include the geographical origin, socio-economic status, tobacco and cannabis consumption, length and weight at birth, birth order, and the familial history of TGCT.

The two control groups will be used first as separate control groups to identify potential major differences. In order to examine whether any of the associations between pesticide exposures and TGCT risk differ by subgroups of known risk factors or by genetic polymorphisms, we will perform additional stratified analyses. Tests for statistical interaction will be used to examine whether any apparent heterogeneity of effect is statistically significant. This will be done by comparing models with and without interaction terms between the risk factor or genetic polymorphisms and the environmental variable (pesticide exposure) with a maximum likelihood ratio test. Sensitivity analyses are planned to explore the impact of potential bias or methodology limitations (such as quality of satellite images, through removing subject born before 1986 having less precise satellite images at time of birth).

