### Study population

The study population consists of men aged 18 to 44 years at date of diagnosis, born in metropolitan France, with a valid health insurance affiliation. Cases are men diagnosed with seminoma or non-seminoma TGCT (ascertained through histological report), and seen in one of the participating CECOS for sperm cryopreservation. Controls of group A are sperm donors or partners of infertile women having a normal sperm count (>39 million per ejaculate [37]). Controls of group B are partners of pregnant women hospitalized for a pathological pregnancy in the level III maternity (regional maternity) adjacent to the CECOS. Participants have to sign an informed consent form. Subjects unable to write and understand French language, as well as subjects presenting severe psychological or mental disorders, and subjects under legal guardianship are excluded. Controls with a history of cryptorchidism or of TGCT are also excluded. Two controls (one of each group) are matched to each case on age (±2 years) and the recruiting center.

Considering the incidence of TGCT and the CECOS activity, we estimate a 18-month duration to recruit all cases and controls. The recruitment is performed by physicians and/or midwives (investigators). A written permission is asked to cases and controls to contact their mothers (or the closest relative alive, if the mother is deceased or cannot be interviewed). Participants who sign the informed consent receive a document to prepare information prior to the phone interview, including: lifetime residential history, addresses of schools during childhood, parental occupation at subjects’ conception, birth information, and job history. Investigators propose to each case and control to participate in a blood sample collection. Information on subjects is recorded using a protected on-line study platform that generates a unique identification number for each participant. Cases and controls receive a financial compensation for their participation: 20 euros for completion of the interview and 40 euros for participation in both blood sampling and completion of the interview.

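### Choosing confounders one by one by change in the odds ratio can leave joint confounding in the final model and cannot separate a confounder from a mediator

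*Protocol article*

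**What the plan says.** Under Statistical analyses, the protocol article sets the model: "Risk analyses will be based on conditional logistic regression models". Matching is described under Study population: "Two controls (one of each group) are matched to each case on age (±2 years) and the recruiting center". Factors beyond the matching criteria "will be examined and added to the model one by one". The effect of each is then judged by setting the model that contains it against the model that does not. The retention rule is that "only factors with relevant changes in the odds ratios will be kept in the final model".

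The candidates are given as an open list: "Potential confounders include the geographical origin, socio-economic status, tobacco and cannabis consumption, length and weight at birth, birth order, and the familial history of TGCT". Counting tobacco and cannabis separately, and likewise length and weight, that makes eight.

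The article does not say how large a relevant change is, or whether each factor is compared alone with the unadjusted model or added cumulatively. It names no fixed adjustment set. The two control groups are first to be analysed separately.

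**The concern.** A change-in-estimate rule applied factor by factor judges each variable by its own effect on the odds ratio. Confounding adds up across factors, but the rule never looks at the sum. If eight factors each move the estimate by 3%, all eight may be dropped and the whole of their joint effect stays in the reported odds ratio.

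The rule is also blind to causal role. The main objective concerns prenatal and early childhood exposure. Length and weight at birth are determined after prenatal exposure and may lie on its pathway to disease. A mediator moves the odds ratio just as a confounder does, so the rule would keep it for the wrong reason.

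Finally, nothing in the rule prevents different covariates from being kept for control groups A and B. The Discussion treats agreement between the groups as support for the hypotheses, so a difference that comes only from different adjustment would be misread.

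**Working it through.** **1. The plan's own figure.** Inputs from Determination of the sample size: 500 cases, 1000 controls, 10% exposed, 5% significance (taken as two-sided), odds ratio 1.6.

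- Exposure in cases: 1.6 × 0.10 / (1 + 0.6 × 0.10) = 0.1509. Pooled: (0.1509 + 2 × 0.10)/3 = 0.1170.
- Null SE: √(0.1170 × 0.8830 × (1/500 + 1/1000)) = 0.0176.
- Alternative SE: √(0.1509 × 0.8491/500 + 0.10 × 0.90/1000) = 0.0186.
- z = (0.0509 − 1.96 × 0.0176)/0.0186 = 0.88, so power is about 81%.

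Solving for 80% power gives a detectable odds ratio of 1.59 at 10% exposed and 1.49 at 15%. The stated 1.6 and 1.5 are reproduced.

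**2. Why one-by-one screening misses joint confounding.** For an independent standardised factor with log odds ratio *a* on exposure and *g* on disease, the shift in the exposure log odds ratio is roughly *a* × *g*. With 1.2 per SD on both:

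- one factor: (ln 1.2)² = 0.0332, a change of about 3.4%, below a 5% or a 10% threshold;
- eight factors: 8 × 0.0332 = 0.266, an odds ratio of about 1.30.

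**3. Simulation.** 500 replicates per setting; 500 sets matched 1:2; 10% exposed; true odds ratio 1.0; eight factors acting in the same direction, equally strong on exposure and disease. Factor strength, correlation and thresholds are assumptions; the article gives none.

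| Factor OR per SD | Correlation | Threshold | Rule | Mean OR | Coverage | Mean SE / empirical SD | Kept (of 8) |
|---|---|---|---|---|---|---|---|
| 1.0 | 0 | 10% | each alone | 1.00 | 96.6% | 0.184/0.177 = 1.04 | 0 |
| 1.1 | 0 | 10% | each alone | 1.07 | 93.4% | 0.180/0.187 = 0.96 | 0 |
| 1.2 | 0 | 10% | each alone | 1.28 | 69.4% | 0.172/0.176 = 0.98 | 0.02 |
| 1.2 | 0 | 5% | each alone | 1.17 | 80.4% | 0.176/0.197 = 0.89 | 1.4 |
| 1.2 | 0 | 5% | cumulative | 1.16 | 81.2% | 0.176/0.198 = 0.89 | 1.5 |
| 1.3 | 0 | 10% | each alone | 1.57 | 24.6% | 0.166/0.191 = 0.87 | 0.6 |
| 1.3 | 0 | 10% | cumulative | 1.55 | 27.2% | 0.166/0.198 = 0.84 | 0.7 |
| 1.2 | 0.2 | 10% | each alone | 1.01 | 93.2% | 0.185/0.196 = 0.94 | 7.4 |
| 1.2 | 0.2 | 10% | cumulative | 1.24 | 74.6% | 0.175/0.199 = 0.88 | 2.1 |

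Adjusting for all eight gave mean odds ratios of 0.99 to 1.01, coverage of 93% to 96% and SE ratios of 0.94 to 1.04. Monte Carlo error is about 1 to 2 points on coverage.

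**4. Direction.** In separate runs with seven factors at log odds ratio 0.18 per SD and a 10% threshold, same-direction factors gave 1.24 with 25% rejection. With four factors one way and three the other, the result was 1.01 with 6% rejection (1.04 and 11% at a 5% threshold).

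**5. Misplaced or too narrow?** In the 1.2 per SD, 10% threshold case the shift is ln 1.275 = 0.243, and 0.243/0.172 = 1.41 standard errors. A correctly sized interval displaced by that much covers with probability about Φ(1.96 − 1.41) = 0.71; the simulation gave 0.694. Displacement explains nearly all of the loss.

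**6. Cost of adjusting for everything.** At true odds ratio 1.6 without confounding, the SE was 0.166 against 0.165 (about 1%). At true 1.0 with factors of 1.2 it was 0.184 against 0.172 (about 7%). With factors of 1.3 it was 0.185 against 0.166 (about 11%), but there the smaller SE belongs to an estimate of 1.57 for a true 1.0. At true 1.6, power with all eight factors stayed at 78% to 83%.

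**The case against.** **The settings are unfavourable by construction.** Independence, common direction and equal strength are assumed, and no part of the article supports them. Some listed factors come in natural pairs, such as tobacco with cannabis and length with weight. With correlation 0.2, testing each factor alone keeps nearly all of them and the bias disappears. This stands: the bias is a possibility, not a prediction. It does not make the rule safe, because under cumulative addition, an equally natural reading of the text, the same correlation left 1.24.

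**A reader might infer that the reported intervals will be too narrow.** The results do not support this as a general statement. Where almost nothing is kept, the width is right (ratio 0.98). Narrowing of about 11% to 16% appears only when selection is active.

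**A reader might take 1.5 to 1.6 as the expected result.** The article gives these as minimum detectable odds ratios and predicts no result. They serve only as a yardstick.

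**A reader might count the missing threshold and order of entry as the error.** An article commonly leaves these to a fuller document. The point rests on the selection rule that is stated.

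**Safeguards exist.** Matching covers age and centre only. Comparing models with and without adjustment is the selection step itself. The planned sensitivity analyses are open-ended, with satellite image quality as the only example. Agreement between control groups does not help if the same confounding affects both.

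**The recommended smaller set was not simulated.** This also stands: the results above are for adjustment for all factors.

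**Conclusion.** The concern holds as a conditional one. The stated rule can leave joint confounding in the final model. With independent, same-direction factors of about 1.2 per SD and 10% exposed, a true odds ratio of 1.0 is estimated at about 1.17 to 1.28 with coverage of about 69% to 80%. On the log scale that is 0.154/0.470 = 33% to 0.243/0.470 = 52% of ln 1.6, the log of the smallest effect the study is sized to detect at that prevalence.

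The bias is slight at 1.1 per SD, absent without confounding, near zero when factors oppose each other, and absent under each-alone testing of correlated factors. Which situation applies cannot be known beforehand. With 500 cases and about eight candidates, sample size gives no reason to screen. The inability to separate a mediator from a confounder does not depend on the simulation assumptions.

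**What to change.** - For each exposure window, name one adjustment set in advance from the listed variables on causal grounds, and use the same set for both control groups.
- Leave length and weight at birth out of the main prenatal-exposure model; add them only as a sensitivity analysis.
- Include tobacco and cannabis consumption in the later-life exposure models. State whose consumption is meant, since Table 1 collects smoking and drug use from both subjects and mothers.
- Report the unadjusted and fixed-set models side by side, and use change in estimate only descriptively.

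This is a change of wording in the analysis plan and uses information the study already intends to collect. The cost is a slightly larger standard error: about 1% to 7% when all factors are adjusted for and factor strengths are no more than 1.2 per SD. The smaller set was not simulated, and it does not control for variables left out of it. Some subjects will also be lost through missing covariates; the Discussion cites mothers' participation of 54% to 71%, although sons report some of the same items. In matched sets, a missing value in the case removes the whole set.

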## Background

Testicular Germ Cell Tumors (TGCT, testicular cancer) represent the most frequent cancer in young men aged 15 to 45 years in developed countries with primarily Caucasian populations. TGCT incidence has been increasing throughout Europe over the last 30 years, including in France, where the annual incidence rate has doubled from 3.4/100 000 in 1980 to 7/100 000 in 2008 [1–3]. Large geographical variation in incidence rates exists between different European countries with West–east and North–south gradients [2, 4]. The reasons for such a phenomenon are still unclear but a role of environmental factors is strongly suspected. The rapid increase of TGCT incidence rates and the evolution of the incidence rate in migrant populations [5, 6] support this hypothesis. However, TGCT risk varies also by ethnicity (Caucasian men have a higher TGCT risk than men in Asian or African populations) [7], and familial history of TGCT is also known to be associated with an increased TGCT risk [8], supporting a potential role of genetic factors. It is estimated that 13% of TGCT have a genetic origin [8]. Individual factors have also been suggested to be associated with TGCT risk [9, 10] and several studies have suggested a positive association between a higher socioeconomic status and TGCT occurrence [11–13], although this relationship was not consistently found [14].

Given the peak incidence of TGCT in very young adults and the fact that TGCT has been shown to develop through carcinoma-in situ cells of fetal origin [15], the role of early exposures, in particular during the critical time windows when the reproductive tract develops has been hypothesized [16, 17]. The concept of the Testicular Dysgenesis Syndrome (TDS) proposes that an impaired development of fetal testes may lead to an increased risk of cryptorchidism, hypospadias, testicular cancer and decreased spermatogenesis [17, 18]. However, the TDS incidence in the general population is unknown and to what extent these disorders are actually biologically related through a fetal mechanism remains unresolved. Although the concept of TDS remains controversial [19, 20], the hypothesis of a pre-natal origin of TGCT and a role of in-utero or early childhood exposures to environmental factors in TGCT development remain widely accepted. A combined effect of prenatal, early and later-life (adolescence or adulthood) exposures has also been suggested [21], but has not been explored so far.

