### Objectives

Our case–control study aims to assess the impact of multisource pesticides exposure (domestic, occupational and environmental) during prenatal and early childhood periods on the risk to develop a TGCT during adulthood. The study is also designed to assess potential gene-environment interactions as well as the hypotheses of combined prenatal and later life exposure.

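### Birth length and weight can enter the final prenatal-exposure model under the change-in-odds-ratio rule, and its odds ratio would then not be the total effect of prenatal exposure

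*Protocol article*

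**What the plan says.** The Objectives section gives the aim as the impact of pesticide exposure from several sources "during prenatal and early childhood periods on the risk to develop a TGCT during adulthood". The Background describes as widely accepted "the hypothesis of a pre-natal origin of TGCT and a role of in-utero or early childhood exposures to environmental factors in TGCT development".

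Under Statistical analyses, exposure is split into PEPPP (before and soon after birth) and PEA (adolescence): "We will examine PEPPP exposure, PEA exposure, and combined PEPPP and PEA exposure in relation to TGCT risk". The potential confounders are geographical origin, socio-economic status, "tobacco and cannabis consumption, length and weight at birth, birth order, and the familial history of TGCT". Candidate factors "will be examined and added to the model one by one". Models with and without each are compared, and "only factors with relevant changes in the odds ratios will be kept in the final model". This list and rule are written for pesticide exposure in general, with no distinction by window.

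On timing, the Environmental exposure assessment section states: "Cases and controls residential history are gathered from 1 year prior to birth to date of the inclusion in the study". Table 1 takes the father's job history from a year before conception. The same table lists "Smoking status; Drug use" for sons and for mothers alike.

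**The concern.** A confounder of prenatal exposure must act before that exposure, or at least not result from it. Birth length and weight do not clearly meet that condition. They are fixed at the end of the window in which the exposure acts, and the study's own hypothesis is that the exposure acts on the fetus. They may therefore carry part of the effect. They may also be colliders: if an unmeasured fetal factor influences both birth size and TGCT, conditioning on birth size links the exposure to that factor.

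A change-in-estimate rule looks only at how far the odds ratio moves. A mediator moves it too, and the more of the effect it carries, the more it moves it. The rule is thus most likely to keep birth size when keeping it removes most of the effect. At stake is the meaning of the odds ratio for the study's main question.

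**Working it through.** **1. The plan's own figure.** Inputs from Determination of the sample size: 500 cases, 1000 controls, 80% power, 5% significance (two-sided assumed), exposure prevalence p0 of 10% or 15%. Prevalence in cases is p1 = p0 × OR / (1 + p0 × (OR − 1)).

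- p0 = 0.10, OR 1.6: p1 = 0.16 / 1.06 = 0.1509. A two-proportion calculation with two controls per case needs 485 cases; power with 500 is 81.2%; the smallest detectable OR is 1.59.
- p0 = 0.15, OR 1.5: p1 = 0.225 / 1.075 = 0.2093. This needs 484 cases; the smallest detectable OR is 1.49.

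The stated 1.6 and 1.5 reproduce, and the sample size is not at fault.

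**2. Order in time.**

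| Exposure | Relation of birth size to it | Status of birth size |
|---|---|---|
| Prenatal part of PEPPP | after | possible intermediate or collider |
| Early postnatal part of PEPPP | before | possible confounder |
| PEA | before | possible confounder |
| Combined PEPPP and PEA | after one part, before the rest | both at once |

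The article applies one rule to all four rows.

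**3. What adjustment could do.** The documents give no effect of pesticides on birth size and none of birth size on TGCT, so both are assumed. Take a total OR of 1.6, an exposure that lowers birth size by d SD, and a TGCT odds ratio m per SD lower birth size. For a rare disease without interaction, adjusted OR ≈ 1.6 / exp(d × ln m). The share of the log OR removed is d × ln m / ln 1.6, with ln 1.6 = 0.4700. The simulation column comes from unmatched case-control data fitted with and without birth size. Power is for 500 cases and 1000 controls at 10% prevalence if the OR were the adjusted value.

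| d | m | d × ln m | Adjusted OR | Change in OR, formula | Change, simulation | Share of log OR removed | Power |
|---|---|---|---|---|---|---|---|
| 0.1 | 1.1 | 0.0095 | 1.585 | −0.9% | −1.1% | 2.0% | 79.5% |
| 0.2 | 1.3 | 0.0525 | 1.518 | −5.1% | −5.4% | 11.2% | 70.9% |
| 0.2 | 1.5 | 0.0811 | 1.475 | −7.8% | −7.9% | 17.3% | 64.5% |
| 0.4 | 1.3 | 0.1049 | 1.441 | −10.0% | −9.7% | 22.3% | 58.8% |
| 0.4 | 1.5 | 0.1622 | 1.360 | −15.0% | −14.9% | 34.5% | 44.8% |

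The article sets no numerical meaning for a relevant change. A threshold above 15% would keep birth size in none of these cases; a threshold below 0.9% would keep it in all. Any threshold in between keeps it in the lower rows, where the loss is larger.

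**4. Opposite signs.** If the birth-size path runs against the rest of the effect, the same formula with the sign reversed gives 1.6 × exp(0.0095) = 1.615 up to 1.6 × exp(0.1622) = 1.882. Adjustment then moves the OR away from 1. The collider path is left without a number, because its size and sign depend on an unmeasured factor.

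**The case against.** The best defence is that the list names candidates only, that a change must be relevant before a factor is kept, and that models are compared with and without adjustment, so an estimate free of birth size will exist. Birth size is a proper candidate for postnatal and adolescent exposure, which the same list serves. It might also stand in for earlier maternal or fetal causes that do confound. Window-specific covariate sets may sit in a full protocol or analysis plan that is not shown.

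Much of this stands and narrows the point. Birth size is not kept at any change, however small, and the fault does not extend to PEA or to the postnatal part of PEPPP. What remains is that the published rule is explicit, holds no criterion of timing or cause, and decides which model is final. The comparison without birth size serves as a screening step, not as the result. If window-specific sets exist elsewhere, the point is answered by citing them.

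Two further readings are tempting but not supported. A reader might infer that the tobacco and cannabis entry means the son's own later use. The article does not say whose use is meant, and Table 1 collects smoking and drug use from mothers too. A reader might also infer that covariates will be chosen separately for control Groups A and B, giving odds ratios that are not like for like. The article says only that the groups are first used separately to look for major differences.

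**Conclusion.** The concern holds for prenatal exposure and for the prenatal term of combined models. As written, the rule can put birth length or weight in the final model, and the odds ratio reported there would not be the total effect.

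The size is unknown. On the assumed inputs, a total OR of 1.6 becomes 1.585 to 1.360, from a negligible loss to about a third of the log OR. If exposure does not affect birth size, there is no mediated effect to lose. A reader might infer that the bias always runs toward or below 1; that depends on signs the documents do not give. Nor does the power column show that the study is too small: it only expresses the possible attenuation in the study's own terms.

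**What to change.** State in the analysis plan, before analysis:

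- For prenatal exposure, and for the prenatal term of combined PEPPP and PEA models, the model without birth length and weight is primary. The birth-size-adjusted model is reported as a labelled secondary analysis.
- Covariates for each exposure window are chosen on timing and causal grounds, not by change in the odds ratio alone.
- Birth size may remain a candidate confounder for purely postnatal exposure and for PEA.
- The plan says whose tobacco and cannabis use is meant. If it is the son's own, it is left out of the prenatal models. Maternal smoking may be used there if the recorded timing is prenatal, which Table 1 does not show.
- The same covariate set is used with Groups A and B, because the Discussion draws weight from agreement between them.

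The cost is wording and one extra secondary model. No new data are needed, and the detectable odds ratios of 1.6 and 1.5 stand.
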